## Abstract

**Background:**

Entertainment-education media can be an effective strategy for influencing health behaviors. To improve entertainment-education effectiveness, we seek to investigate whether the social authority of a person delivering a health message arouses the motivation to reject that message—a phenomenon known as reactance.

**Objective:**

In this study, using a short animated video, we aim to measure reactance to a sugar reduction message narrated by a child (low social authority), the child’s mother (equivalent social authority to the target audience), and a family physician (high social authority). The aims of the study are to determine the effect of the narrator’s perceived social authority on reactance to the sugar reduction message, establish the effectiveness of the video in improving behavioral intent to reduce the intake of added sugars, and quantify participants’ interest in watching the entertainment-education intervention video.

**Methods:**

This is a parallel group, randomized controlled trial comparing an intervention video narrated by a low, equivalent, or high social authority against a content placebo video and a placebo video. Using a web-based recruitment platform, we plan to enroll 4000 participants aged between 18 and 59 years who speak English and reside in the United Kingdom. The primary end points will include measures of the antecedents to reactance (proneness to reactance and threat level of the message), its components (anger and negative cognition), and attitudinal and behavioral intent toward sugar intake. We will measure behavioral intent using list experiments. Participants randomized to the placebo videos will be given a choice to watch one of the sugar-intervention videos at the end of the study to assess participant engagement with the entertainment-education video.

**Results:**

The study was approved by the ethics committee of Heidelberg University on March 18, 2020 (S-088/2020). Participant recruitment and data collection were completed in December 2020. The data analysis was completed in April 2021, and the final results are planned to be published by August 2021.

**Conclusions:**

In this trial, we will use several randomization procedures, list experimentation methods, and new web-based technologies to investigate the effect of perceived social authority on reactance to a message about reducing sugar intake. Our results will inform the design of future entertainment-education videos for public health promotion needs.

**Trial Registration:**

German Clinical Trials Registry DRKS00022340: https://www.drks.de/drks_web/navigate.do?navigationId=trial.HTML&TRIAL_ID=DRKS00022340.

**International Registered Report Identifier (IRRID):**

DERR1-10.2196/25343

## Introduction

### Background

Entertainment-education media can be an effective strategy for influencing health behaviors [1-3]. However, entertainment-education media face the same challenges as other traditional persuasion methods [4]. Persuasive health messages often fail to achieve the desired effect [5], and in some cases, may arouse the motivation to reject a message, a phenomenon known as reactance [6].

The theory of reactance comprises 4 elements [6]: (1) freedom, which individuals possess insofar as they are aware of it and can enact it; (2) threat to freedom, which involves any pressure on the individual, making it more difficult to enact that freedom; (3) reactance, which is the motivation to re-establish the freedom if that freedom is eliminated or threatened with elimination; and (4) direct restoration, which involves the freedom of the individual to perform a forbidden act. Research in this field has led to the development of several strategies to reduce reactance to health messages pertaining to littering [7], use of e-cigarettes [8], use of alcohol [9], and eating behaviors [10], among other health-related messages [11-16].

We are particularly interested in the effect of social authority on reactance to persuasive health messages. Our starting assumption is that an agent (human or otherwise) that delivers a health message possesses some influence or social authority [17]. For example, persons who have high social authority, such as experts or doctors, are often recruited to promote health messages [18-20]. However, research has shown that individuals may perceive health messages from experts as coercive, threatening, or having an ulterior motive [21], which could provoke reactance and negate the impact of the intervention [22,23].

### Objective

In a web-based entertainment-education video setting, there is limited, high-quality experimental evidence on the relationship between reactance and the perceived social authority of a message agent. Using a randomized controlled trial (RCT), we will evaluate the effect of social authority status on reactance to a short animated video on the intake of added sugars. The sugar message will be narrated by either (1) a preadolescent daughter, who has low authority status relative to the other narrators, (2) the daughter’s mother, who has equivalent social authority to the target audience, or (3) the family physician, who is an expert with high social authority. Results from this study will facilitate the development of videos for reducing reactance and improve the persuasiveness of health messages in web-based settings.

This study aims to achieve the following objectives:

Determine the effect of the narrator’s social authority (daughter, daughter’s mother, or family physician) on reactance to a sugar reduction message.Establish the video’s effectiveness in improving behavioral intent to reduce the intake of added sugars.Quantify participants’ interest in watching a short animated video about reducing the intake of added sugars.

Our null hypothesis is that the social authority of the child, who has low perceived social authority, the mother, who has equivalent perceived social authority, or the family physician, who has high perceived social authority, will have no effect on reactance to a video about reducing sugar intake.

## Methods

### Trial Design

This study consists of a parallel group RCT. Participants will be randomized to 1 of 5 arms: either the same sugar-intervention video narrated by a preadolescent daughter (arm 1: low social authority), the daughter’s mother (arm 2: equivalent social authority), or a family physician (arm 3: high social authority), or a content placebo video with a health message about tanning and sunscreen (arm 4: no sugar message), or a placebo video about earthquakes (arm 5: no sugar or health message). We will randomize the participants in a 1:1:1:1:1 ratio to the trial arms. Participants will watch 1 video once from start to finish.

Nested in each of the five trial arms is a list experiment. For each list experiment, participants will be randomized at a 1:1 ratio to a control or treatment group. The control group will receive a list of 5 items about behavioral intent (unrelated to sugar consumption). The treatment group will receive the same 5 items and a sensitive item about behavioral intent to reduce sugar intake. We will use the list experiment to reduce social desirability bias, as participants may already be primed to answer favorably to questions about sugar consumption.

At the end of the study, participants assigned to the content placebo (*arm 4*) or placebo (*arm 5*) will be given a choice to watch the video intervention. Their choices will be recorded. Participants who choose to watch will be randomized at a 1:1:1 ratio to the sugar video narrated by the daughter, mother, or physician. The complete trial flowchart is presented in Figure 1.

**Figure 1 figure1:**
[figure not shown]
Trial design.

### Study Setting

The study setting will be on the internet. We will use the web-based recruitment platform Prolific [24] to enroll study participants. We host and deploy our study on a web-based platform called Gorilla [25], a cloud platform that provides versatile tools for web-based, experimental, and behavioral research [26].

### Eligibility Criteria

Eligibility criteria included being between the ages of 18 and 59 years (male, female, or other), being able to speak English, and being a resident in the United Kingdom; not being eligible according to any of the inclusion criteria was the exclusion criteria. We will not exclude participants on an existing health condition (eg, diabetes) because Prolific does not collect health information from its users.

### Who Will Take Informed Consent?

The participants will undergo a process of informed consent. The consent form, which will be hosted on the Prolific platform, explains the purpose of the study, the risks and benefits of the research, and how a participant can contact the researcher or the human subjects review board at Heidelberg University. By clicking a link, participants will consent to participate in the study and will be redirected to the Gorilla platform. The Gorilla landing page contains additional information about the platform. Participants can exercise their freedom to not participate at any point during the study.

### Interventions

#### Intervention Description

The intervention consists of an entertainment-education video about reducing sugar intake [27-29]. Developed by our coauthor (MA) at the Stanford School of Medicine, the sugar video is animated and designed for a diverse and global audience. The 2 main characters, a mother and her preadolescent daughter, engage in food-related activities, such as grocery shopping and cooking dinner. The video presents educational content on health problems associated with consuming added sugars in foods, such as yogurt, chocolate milk, and breakfast cereals; a review of the World Health Organization recommendations for the daily consumption of added sugars is included. The narrative also includes the story of the father in this family, who dies from diabetes-associated complications because of frequent consumption of soda drinks. It concludes with a text message from the World Health Organization regarding the maximum number of teaspoons of sugar per day.

#### Explanation for the Choice of Comparators

We will compare the 3 intervention videos (*arms 1-3*) with each other (pairwise) to determine which social authority status is associated with the largest change in reactance and behavioral intent to reduce the intake of added sugars. In addition, we will compare the 3 intervention videos with the content placebo video (*arm 4*) and the placebo video (*arm 5*).

The content of the placebo video is similar in style to the sugar video. It is also animated, with a duration of 3.42 minutes, and has a health message about tanning and using sunscreen [30]. We used the content placebo video to isolate the *content effect* of the sugar-intervention video. It is possible that any video with a health message (eg, sunscreen protection) can improve overall health awareness and thus increase behavioral intent to reduce sugar intake. As both the intervention and content placebo videos have a health message, we expect that a significant difference in behavioral intent between the 2 videos (after random assignment) can be attributed to the content of the sugar message.

We will also compare each sugar-intervention video with a placebo video. The placebo describes the causes and characteristics of earthquakes [31] and contains no health-related or sugar consumption content. A significant difference in behavioral intent to reduce sugar intake between the content placebo and placebo videos (after random assignment) can therefore be attributed to the content of the sunscreen message. We call this difference the *health awareness effect*. We describe the *total intervention effect* as the difference between the sugar-intervention and the placebo videos, which is the sum of the content and health awareness effects.

We will also implement a list experiment in each arm with the control list as the comparator. The control list will include 5 items about general behavioral intent. The treatment list will include the same 5 control items plus a sixth item about behavioral intent toward reducing sugar intake. The control list (comparator) is needed to measure the prevalence of behavioral intent to reduce sugar intake, described in the *Behavioral Intent* section.

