### Strengths and Limitations

In a systematic review, Shen and Han [4] concluded that there is a lack of experimental methods to evaluate the effectiveness of entertainment-education media. They call for “controlled experiments to uncover the cognitive and/or affective factors that mediate entertainment-education’s effects” [4]. Our protocol responds to this call by leveraging experimental methods and carefully considering several factors that may mediate the role of social authority on reactance to the sugar reduction message, which we discuss below.

First, our study will use an RCT design to randomize participants to 1 of 3 sugar-intervention videos, a content placebo video, or a placebo video. The 3 intervention videos are exactly the same, except that the sugar message is narrated by the daughter, the daughter’s mother, or the family physician. The RCT should ensure that the enrollment stage does not introduce systematic differences between trial arms. For example, participants may have pre-existing health conditions, such as diabetes, which could affect their responses to the survey questions. However, random assignment will take care of this potential source of bias by distributing it uniformly across trial arms. Thus, holding all else equal, and because of randomization, differences in reactance toward the sugar message should be because of the experimental manipulation of the narrator’s social authority.

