We do not believe that the differences between the placebo videos (which we did not create) and the sugar-intervention videos (which we created) will confound our results. Such differences may relate to the animation style, background shapes or colors, and target audience, among other design decisions. As mentioned, the main interest of our study is the difference in state reactance toward the sugar reduction message following random assignment to the 3 social authority levels. On the basis of the theoretical model described earlier, it is only the content of the message or the characteristics of the messenger that can threaten an individual’s freedom and arouse reactance. As the placebo video of earthquakes does not promote a health message, we expect it to arouse a very small (or even null) level of state reactance (the type of animation style of the placebo videos, for example, cannot realistically threaten an individual’s *freedom*). Therefore, the placebo video will provide a baseline measure of state reactance, which will enable us to quantify the content and health awareness effects. Further, we were very careful to select a content placebo video in which the messenger had culturally neutral or agnostic characteristics. In this case, the narrator of the sunscreen message is not seen, and it is not possible to determine his social authority. A possible exception is that the placebo videos are narrated by male voices and the sugar-intervention videos by female voices. However, it is unlikely that this design difference will be sufficiently large to bias our results significantly.

Third, we will conduct a list experiment in each of the 5 arms. This is the second experimental method that we leverage in our study design. We use a list experiment to reduce social desirability bias in participants’ responses to the behavioral intent questions about reducing sugar intake.It is likely that participants will already be primed to give socially acceptable responses to questions about their health and sugar consumption. The indirect questions (ie, how many statements do you agree with) provide protection to participants if they want to reject the sugar message without revealing this intention. To the best of our knowledge, few (if any) studies have used a list experiment approach to evaluate the effectiveness of an entertainment-education video to improve a given health outcome.

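### The sugar-versus-sunscreen difference in behavioral intent is credited to sugar content, but it also contains the change of narrator

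*Protocol article*

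**What the plan says.** All places are in the Protocol article.

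- **Explanation for the Choice of Comparators, first paragraph.** The three sugar videos are compared pairwise to find which authority status goes with the largest change in reactance and in intent. Each is also compared with the sunscreen video (arm 4) and the earthquake video (arm 5).
- **Same section, second and third paragraphs.** Because the sugar and sunscreen videos both carry a health message, the authors expect that "a significant difference in behavioral intent between the 2 videos (after random assignment) can be attributed to the content of the sugar message". The total intervention effect (sugar minus earthquake) is defined as this content effect plus the health awareness effect (sunscreen minus earthquake).
- **Outcome Measures, Overview.** Behavioral intention is modelled as a consequence of reactance.
- **Strengths and Limitations, on the sugar videos.** "The 3 intervention videos are exactly the same, except that the sugar message is narrated by the daughter, the daughter’s mother, or the family physician".
- **Strengths and Limitations, on the decomposition.** The same three-part split is set out for mean state reactance, with the same attribution to sugar content.
- **Strengths and Limitations, on the comparators.** "the narrator of the sunscreen message is not seen, and it is not possible to determine his social authority". Also, "the placebo videos are narrated by male voices and the sugar-intervention videos by female voices". The authors judge the voice difference unlikely to bias the results. On reactance, they state that "it is only the content of the message or the characteristics of the messenger that can threaten an individual’s freedom and arouse reactance".

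**The concern.** A contrast can be credited to one ingredient only if the two videos are alike in every other ingredient that could move the outcome. Here the narrator changes along with the topic, and the narrator is the factor that this trial was designed to study. In arms 1 to 3 the narrator's authority is set by design; in arm 4 it is unknown, and the voice is of the other sex.

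At stake is the reading of objective 2, whether the video improves intent to reduce added sugar. A significant sugar-versus-sunscreen difference would be reported as the effect of sugar content when some or all of it could come from who was speaking. The same holds for the reactance version of the split in Strengths and Limitations.

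**Working it through.** The plan gives no figure for this contrast or for a narrator offset, so there is nothing to reproduce. The check is to write out what each contrast contains.

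**Set-up.** For one list experiment, let P_j be the estimated prevalence in arm j (mean of the treatment list minus mean of the control list, as in Statistical Methods). Let S, H and E be the contributions of sugar, sunscreen and earthquake content, and N_j the contribution of the narrator in arm j. Additivity is an assumption made for clarity; the protocol states no such model.

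- Arms j = 1, 2, 3: P_j = base + S + N_j
- Arm 4: P_4 = base + H + N_4
- Arm 5: P_5 = base + E + N_5

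**Contrasts.**

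| Protocol label | Contrast | What it contains |
|---|---|---|
| Content effect | P_j − P_4 | (S − H) + (N_j − N_4) |
| Health awareness effect | P_4 − P_5 | (H − E) + (N_4 − N_5) |
| Total intervention effect | P_j − P_5 | (S − E) + (N_j − N_5) |
| Narrator comparison | P_j − P_k, both in arms 1–3 | N_j − N_k |

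The content effect equals the content difference S − H only if N_j = N_4. The first two rows add to the third whatever the values. No sugar narrator enters the second row, and content cancels in the fourth.

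**Does the protocol allow N_j = N_4 to be assumed?** Set side by side, its own statements point the other way:

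1. The comparators section looks for the authority status with the largest change in intent, so the narrator is treated as a possible cause of intent.
2. Strengths and Limitations names messenger characteristics as able to arouse reactance, and the Overview makes intent a consequence of reactance. Together these give a route from narrator to intent.
3. Principal Findings records that the designers considered that a child's lack of expertise might cancel the persuasiveness of the message.
4. The arm 4 narrator's authority is said to be undeterminable, so N_4 cannot be matched to any of N_1, N_2 or N_3.

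**Numbers (illustrative assumptions, not from the plan).** Offsets are N_j − N_4 for arms 1, 2 and 3.

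| Content difference S − H | Offsets | Reported content effects | Mean of the three |
|---|---|---|---|
| 0.10 | 0, 0, 0 | 0.10, 0.10, 0.10 | 0.10 |
| 0.10 | −0.05, 0, +0.05 | 0.05, 0.10, 0.15 | 0.10 |
| 0.10 | +0.05, +0.05, +0.05 | 0.15, 0.15, 0.15 | 0.15 |
| 0 | +0.05, +0.05, +0.05 | 0.05, 0.05, 0.05 | 0.05 |

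The last two rows matter most. An offset common to the three sugar arms is invisible in the comparisons among them and survives averaging. In the last row the whole reported effect comes from the narrator. Voice sex is such a common element: it is female in arms 1 to 3 and male in arms 4 and 5.

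**The case against.** **The issue is disclosed.** Strengths and Limitations states that the sunscreen narrator is unseen, that his authority cannot be determined and that voice sex differs, and the attribution is introduced as an expectation. That stands: nothing is hidden. But the voice difference is dismissed without data, and the section presents undeterminable authority as an advantage without asking what it does to the sugar-versus-sunscreen contrast. The argument that animation style cannot threaten freedom concerns reactance and does not cover the narrator.

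**The remark on messenger characteristics is also about reactance.** This is right, and taken alone it would not carry over to intent. The link comes from the Overview model and, more directly, from the stated aim of comparing narrators on intent.

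**Randomization takes care of it.** It balances participants between arms. It cannot separate features that travel together in one video.

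**Narrator-specific effects of one message are effect modification, not an error.** This stands. A reader might infer that three different content effects from identical content would contradict the plan. They would not, since narrator-specific results are what the trial is looking for. The crediting of differences among arms 1 to 3 to the narrator also holds whatever the size of the narrator effect. The fault lies in the comparison with arm 4.

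**Stronger readings that the documents do not support.** A reader might infer that the whole decomposition fails. It does not: the health awareness effect involves no sugar narrator, and the sum is an identity. A reader might also infer that the article promotes the split of intent as its innovative feature, or that success on objective 1 would by itself disprove the label for intent. The innovation remark belongs to the placebo videos and the split of mean state reactance, and both the stated null hypothesis and objective 1 concern reactance.

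**Conclusion.** The attribution rule is wrong as written. On the protocol's own account of what can move intent, each sugar-versus-sunscreen difference mixes sugar content with a change of narrator, and the design cannot separate them. The same limit applies to the total intervention effect and to the parallel attribution for mean state reactance.

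The error equals the narrator offset, one for one. Its real size and sign are unknown: the documents give no figure, and the values in the tables are illustrative. The conclusion does not depend on additivity. If content and narrator interact, the contrast is still a joint effect of both.

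Each contrast remains a valid randomized comparison of whole videos, and the planned regression need not change. The comparisons among arms 1 to 3, which the article calls its main interest, are unaffected. A finding of no difference among those arms would not rescue the label, because a common offset from the sunscreen narrator could remain.

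**What to change.** 1. In Explanation for the Choice of Comparators, name each contrast as the sugar video with narrator X versus the sunscreen video, and replace the attribution to sugar content with a claim about the video as delivered by that narrator. Qualify the total intervention effect in the same way.
2. Make the same change where Strengths and Limitations applies the attribution to mean state reactance.
3. If a single figure is wanted, report the mean of arms 1 to 3 minus arm 4 as a whole-video contrast. State that it contains content, narrator and voice sex together, and that averaging does not remove an offset common to the three narrators.
4. Restrict the statement that voice sex is unlikely to bias the results to the comparisons among arms 1 to 3, where all voices are female.

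The cost is a less specific causal claim. No new data, arm or model is needed.

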##### Behavioral Intent

The behavioral intent to reduce the intake of added sugars will be measured using a list experiment approach. In Textbox 2, we present the 6 experiments and their list items. The control group will receive a list of 5 items, whereas the treatment group will receive the same list but with 1 additional sensitive item. The sensitive item covers the topics of natural versus added sugar, consumption of sugar-sweetened beverages, fresh fruit intake, reading of sugar content on package labels, teaspoons of sugar consumed per day, and home cooking.

We will assess whether participants are motivated (in lists 1, 3, and 4) or unmotivated (in lists 2, 5, and 6) to undertake the sensitive item. For example, in list 1, imagine that the control group selects an average of 2 out of the 5 items, and the participants in the treatment group select an average of 2.2 out of the 6 items. Holding all else equal, we conclude that the prevalence of participants who would cut their daily intake of sugar is 20%. The intention to restore one’s freedom will be present if there are higher scores for the *unmotivated* lists in the treatment group than the control group. The intention to reduce sugar intake will be present if there are higher scores for the *motivated* lists in the treatment group than the control group.

To avoid alerting the participant to the purpose of the list experiment and order effects, the 6 list experiments will be presented in random order. We designed the items to minimize ceiling and floor effects [42]. As described in the *Statistical Methods* section, we will use regression models to estimate the prevalence of each sensitive item [43]. These data will be used to assess objective 2.

List experiment items. Each list experiment will be preceded by the question “How many of the five/six statements do you agree with? We don’t want to know which ones, just answer how many. This week I feel motivated/unmotivated to...”

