### Statistical Methods

#### Statistical Methods for Primary and Secondary Outcomes

For the descriptive statistics, we will obtain means and SDs of age, sex, country of residence, and education status variables. We will use an analysis of variance to estimate pairwise differences in means between the sugar-intervention videos, content placebo video, and placebo video. We will use the Tukey range method to create confidence intervals for all pairwise differences between the means while controlling for the family error rate. Within each trial arm, we will estimate the prevalence of behavioral intent as the difference between the treatment and control list for each list experiment. From these estimates, we will obtain the differences in means between trial arms. This approach is analogous to a difference-in-difference analysis, which we will implement by specifying the main and interaction terms in an ordinary least squares (OLS) regression model. The OLS equation for each list experiment is given as follows:

y = b_0_ + b_1_*VideoArm* + b_2_*TreatList* + b_3_*VideoArm* × *TreatList*

where y is the number of statements in the list that the participant agreed with, *VideoArm* indicates the arm to which the participant was assigned, and *TreatList* indicates if the participant was assigned to the treatment list within that arm. We will calculate standard errors, 95% CIs, and *P* values for linear combinations of coefficients from the OLS model. We will use R statistical software to perform the analysis.

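### Objective 2 asks about one sugar video, but only narrator-by-narrator comparisons with the placebos are stated; adding the narrator-averaged contrast from the planned model would answer it more precisely

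*Protocol article*

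**What the plan says.** The Objective section of the protocol article frames objective 2 around a single object: "Establish the video’s effectiveness in improving behavioral intent to reduce the intake of added sugars". Strengths and Limitations treats the three sugar arms as versions of one film: "The 3 intervention videos are exactly the same, except that the sugar message is narrated by" the daughter, the mother or the physician.

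Explanation for the Choice of Comparators sets the three sugar arms against arm 4 (sunscreen video) and arm 5 (earthquake video), and adds: "We will also compare each sugar-intervention video with a placebo video". It defines a content effect (sugar against arm 4) and a total intervention effect (sugar against arm 5). It does not say whether either is taken per narrator or averaged over narrators.

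Statistical Methods for Primary and Secondary Outcomes plans Tukey intervals for all pairwise differences in means. For the lists, it takes treatment-list minus control-list within each arm, and then: "From these estimates, we will obtain the differences in means between trial arms". The model is an OLS regression for each list with a VideoArm by TreatList interaction. Standard errors, 95% CIs and P values are promised for linear combinations of its coefficients, but the combinations are not named. Under Behavioral Intent, each of the six lists has its own estimate: "we will use regression models to estimate the prevalence of each sensitive item".

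**The concern.** The question concerns the video, while the stated answers concern each narrator. For one list there are 3 narrators x 2 placebos = 6 arm-level contrasts, and the text does not say how they combine into a statement about the video. Two things follow.

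- **Precision.** If the narrators have similar effects, each arm-level contrast uses only a third of the sugar-arm data, so an overall effect is more easily missed.
- **Interpretation.** When the three narrator tests against one placebo fall on different sides of the significance threshold, the natural reading is that the narrator matters. That is objective 1's question, and it should be answered by comparing arms 1 to 3 with each other.

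**Working it through.** **Inputs.** From Sample Size: N = 4000; SDs 0.85 (control list) and 1.0 (treatment list); alpha 0.05; list difference 2.15 - 2.0 = 0.15. From Trial Design: allocation 1:1:1:1:1 to arms and 1:1 to lists, so 4000 / 5 / 2 = 400 per list cell.

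**Assumptions.** No attrition, two-sided 0.05, normal approximation. The protocol uses 0.15 for treatment list against control list and gives no effect for a difference between arms. Using 0.15 and 0.20 on the difference-in-differences scale is therefore an assumption.

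**The plan's own figure.** The article states n = 769 per group. Its formula is not legible in the text at hand. The usual form, with the number of comparisons equal to 2, gives (0.85² + 1.0²) x ((2.241 + 0.842) / 0.15)² = 728. So 769 is not reproduced, but it exceeds 728 and does not affect this point.

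**Standard errors.** The variance of one arm's prevalence estimate is (0.85² + 1.0²)/400 = 1.7225/400.
- One narrator against one placebo: sqrt((1 + 1) x 1.7225/400) = 0.0928.
- Mean of three narrators against the same placebo: sqrt((1/3 + 1) x 1.7225/400) = 0.0758.
- Variance ratio: 2 / (4/3) = 1.5. The single-contrast SE is 22% larger.
- At 769 per arm the SEs are 0.0947 and 0.0773, with the same ratio.

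**Power with the same true effect in all three narrator arms.**

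| Common effect | One narrator vs placebo | Three-arm mean vs placebo |
|---|---|---|
| 0.15 | 37% | 51% |
| 0.20 | 58% | 75% |
| 0.25 | 77% | 91% |

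At 0.15 with the five-arm Tukey critical value (z about 2.73) applied to both, power is 13% against 23%.

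**Mixed results.** Independent arm estimates were simulated with a common effect of 0.15. A trial counts as mixed when one or two of the three narrator tests against one placebo are significant.

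| Critical value | Trials with mixed results |
|---|---|
| 1.96 (unadjusted) | 47% |
| 2.24 (two comparisons) | 40% |
| 2.73 (Tukey, five arms) | 25% |

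Over all effect sizes, the highest rate is about 50%.

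**When narrators differ.** Suppose one narrator has an effect of 0.20 and two have none. The average is 0.20/3 = 0.067, and 0.067/0.0758 = 0.88, so pooled power is about 14%. The effective arm's own contrast has 58%. With two effective narrators the figures are about 42% and 58%.

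**The case against.** Four arguments carry weight.

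1. **The pooled contrast is not excluded.** The linear combinations of coefficients in Statistical Methods would cover it, and the choice of combination is often left to an analysis plan. This stands, so the contrast is unstated rather than ruled out. But the article does more than stay silent: it fixes the comparisons arm by arm, beside an objective about one video.

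2. **The trial exists because narrators may differ.** The Introduction and Discussion give reasons why a physician or a child might weaken the message. The power gain needs similar effects across narrators. This also stands, and the 14% against 58% shows the loss when it fails. It is a reason to keep the narrator-specific contrasts, not to omit the average.

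3. **The two placebos answer different questions.** A result against arm 4 and another against arm 5 may differ without conflict, because the article gives them different meanings. This stands, and the mixed-result rates above therefore use one placebo only.

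4. **Multiplicity.** A reader might infer that the arm-level tests carry inflated false-positive rates. The documents do not support unadjusted rates as the plan's own, because the article names Tukey intervals for all pairwise differences. Whether these extend to the list regressions is unclear, hence the range of critical values.

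A reader might also infer that a common effect will usually produce contradictory verdicts. Against one placebo, mixed significance does not exceed about half of trials at any effect size. A significant result beside a non-significant one is discordance, not contradiction.

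**Conclusion.** The point holds as a cheap improvement in precision and clarity. The comparisons stated for objective 2 do not include the one that matches it. For a narrator-averaged effect, a single arm-level contrast has 1.5 times the necessary variance, and at a common effect of 0.15 the difference in power is 14 percentage points (37% against 51%). At that effect, mixed narrator results against one placebo would arise in about a quarter to just under half of trials with no narrator difference at all.

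These figures rest on 400 per list cell, the protocol's SDs, an assumed effect on the difference-in-differences scale and equal effects across narrators. The planned contrasts are not invalid, and they remain the better tool if only one narrator is effective.

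**What to change.** In Statistical Methods for Primary and Secondary Outcomes, for each list, name two estimates for objective 2 from the existing OLS model:

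- the mean of the VideoArm x TreatList terms for arms 1 to 3 against arm 5 (total intervention effect);
- the same mean against arm 4 (content effect).

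State the beneficial direction: higher for the motivated lists (1, 3 and 4), lower for the unmotivated lists (2, 5 and 6). Report the narrator-specific contrasts with arms 4 and 5 alongside, and use the pairwise comparisons among arms 1 to 3 for the narrator question.

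The cost is a few sentences and two linear combinations per list, with no new data. The downside is dilution when only one narrator works, which is why the narrator-specific results must still be shown. The Results section says the analysis was completed in April 2021, so a contrast introduced now should be labelled as added. The change does not settle how results are combined across the six lists.
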